### Baseline questionnaire

A baseline questionnaire has been developed to provide information to support the evaluation of the BSB interventions. Key components include:Household informationSocioeconomic statusEthnic, cultural and religious backgroundSocial, demographic and family informationNeighbourhoodPhysical and mental healthLanguage and Communication skills including home literacy environmentBehaviour/lifestyle factors including eating habits.

Where available and appropriate, validated questionnaires have been used. Additional sections have been developed based on the BiB cohort questionnaire [16] and through expert opinion of the authors and the local BSB community. The full questionnaire can be seen in Additional file 1. A shortened version of the questionnaire (Additional file 1) will be used where an interpreter is required. The partners questionnaire is a shortened version of the baseline questionnaire used for women and can be seen in Additional file 1.

The baseline questionnaire for women is designed to be partly self-completed and partly administered by a researcher using a tablet device. Researchers will sit with the women while they complete the self-completion questions and will be able to answer any queries. At the end of the questionnaire automated flags will indicate any safeguarding or mental health concerns and the researchers will be prompted to follow standard protocols.

The baseline Questionnaire for partners will be self-completed electronically or via a postal questionnaire.

#### Samples and measurements

Women and partners will consent to the collection of different biological samples and measurements. These are summarised in Table 3 and further details of collection, processing and storage of biological samples can be seen in Additional file 1.

**Table 2 Tab2:** Demographic Information of the Better Start Bradford area compared to Bradford and England

	Better Start Bradford	Bradford district	England
Population (all ages) [34]	65102	528155	54316618
Births per year (rate per 1000 population) [35]	1335 (20)	8100 (15)	661501 (12)
Children 0-3 years (% of the population) [34]	5467 (8.4 %)	32711 (6.2 %)	2748017 (5.1 %)
Ethnicity [36]			
White British	24.8 %	63.9 %	79.8 %
Asian/Asian British: Pakistani	48.6 %	20.4 %	2.1 %
Asian/Asian British: Bangladeshi	5.2 %	1.9 %	0.8 %
Asian/Asian British: Indian	3.8 %	2.6 %	2.6 %
White: Other White	3.7 %	3.0 %	4.6 %
Black	3.2 %	1.8 %	3.4 %
Other ethnicities	10.7 %	6.4 %	6.7 %
Infant mortality rate (per 1000 live births) [37]	^a^ 9.4	7.0	3.6
Decayed, missing, filled teeth (Mean d3mft) age 5 [38]	^b^ 3.6	1.98	0.94
Obesity [39, 40]			
Reception (age 4–5)	11.0 %	8.6 %	9.1 %
Year 6 (age 10–11)	25.7 %	21.5 %	19.1 %

^a^Source: https://www.whatdotheyknow.com/request/infant_mortality_rates_in_bradfo; Provided by a Bradford City Council Public Health Information Analyst in response to Freedom of Information request; data from Better Start Wards are combined to provide IMR per 1000 live births from 2004 to 2012

^b^Ward level data provided by Bradford City Council Public Health

#### Routine data collection

A summary of the planned routine data linkage from health, local authority and BSB interventions can be seen in Fig. 3. Data will be linked by NHS number for healthcare records and BSB intervention data, by Unique Pupil Number (UPN) for education records, and by a unique E-Start number for Children’s Centres. Data sharing protocols will be agreed with all organisations.

**Fig. 3 Fig3:**
[figure not shown]
Routine outcome measures

#### Unique study identifier

Each participant will be allocated a unique identification number which will be used to identify their data throughout the study. Women, their babies and partners will be linked together using a pregnancy identification number. NHS numbers will also be collected for each participant to facilitate data linkage. Families’ attendance at BSB interventions will be tracked using their NHS and UPN numbers. This will allow the cohort to follow families’ journeys through the different interventions. We will use a secure database hosted at the BTHFT to store all of the cohort data on individual children and their parents.

### Retention

As planned follow-up data will all be routinely collected, retention rates will depend on the availability and linkage with routine data. In the BiB study, 86 % of children in Bradford have been linked to schools and over 99 % of mothers and children have been linked with GP records, and the same success rate is expected in BiBBS [18].

To retain families and to keep them engaged, an annual newsletter and birthday card will be sent to each family. This was a successful element of the ongoing BiB cohort, and will be repeated for the new BiBBS cohort. The newsletter will gather the highlights from a BiBBS website over the year, focussing on celebrating key achievements, and findings from the research. Data linkage to GP records ensures that home addresses and the survival status of all participants are regularly updated on the database allowing newsletters and birthday cards to be sent to the most recent address and to be not sent where there has been a recent death.

### Data quality and confidentiality

#### Baseline questionnaire and optional samples/measurements

Researchers will receive formal training from experts in the field of data collection including methods and techniques used in collecting data, practical demonstrations and role play. Data collection will be observed by an independent observer on a regular basis for quality assurance. Researchers will have up to date Good Clinical Practice (GCP) training and will be trained in administering the questionnaire. They will be provided with detailed instructions and background information. Researchers will be supported by the BiB research midwife who will be available for advice and guidance. They will also be trained in BTHFT wide policies on lone working and safeguarding of adults and children.

#### Routine data collection and measurements

Researchers, paediatricians, hospital midwives and health visiting teams in the community will receive regular training on the measures that are included in the cohort. This includes the standard anthropometric techniques needed to assess adult and infant size, assessments of mother-child relationship, maternal depression and anxiety, breastfeeding, routine biological samples and other measures. The training will focus on the importance of reliable data collection and protocols for measurements or assessments in order to reduce error.

All information collected during the course of the cohort will be kept strictly confidential. Information will be held securely on paper and electronically. BiBBS will comply with all aspects of the 1998 Data Protection Act [22]. Wherever possible, consent and baseline questionnaires will be completed electronically using tablet devices. The data collected will be saved onto the BTHFT secure computer server and will not be stored on the local device. Data will only be accessible by authorised members of the BiB team. Data will only be stored with personal identifiers if absolutely necessary. Where electronic data collection is not possible, paper consents and questionnaires will be used and then entered onto the database held within the BTHFT secure computer server. Paper files containing personal identifiers will be stored in locked cabinets within BIHR, separate from all other data.

### Data management

Primary data captured by electronic forms will be synchronised with the cohort database to verify identifiers and validate newly captured data against existing data. Automatic interactive validation will be built into individual data item inputs in electronic forms and questionnaires, such as logical traps, format validations, range limiters and, automated questionnaire flow with mandatory values. Electronic data capture clients for primary data and biosample tracking data will synchronise with the cohort database, from which unattended transform and report functions will provide regular datasets for researchers to analyse to ensure data quality standards are being met. Record matches for routine data linkage will be validated on the basis of unique identifiers (e.g. NHS number) plus multiple non-unique identifiers (e.g. surname, date of birth) where possible. Where unique identifiers are not available, iterative deterministic matching on the basis of multiple sets of non-unique identifiers will be used. The central database, hosted by BTHFT, will store data obtained from all sources listed under *Data Collection*. Data from each source will be linked at the BiBBS person level and will be structured and maintained by BiBBS data managers as a long term strategic store to service cohort data capture, analysis and other research activities as necessary. The entire database schema and data will be backed up nightly. Further details of the data management process can be seen in Additional file 1.

### Methods for analysis

The BiBBS experimental cohort design will enable evaluation of the BSB interventions using both experimental and quasi-experimental methods, in addition to traditional epidemiological approaches to the analysis of observational cohort data.

#### Randomised controlled trials within the cohort

The BiBBS cohort will form a platform to assess the effectiveness of a selection of BSB interventions using a randomised controlled Trials within Cohorts design (TwiCs; also called the cohort multiple randomized controlled trial design) [15]. TwiCs are randomised controlled trials that are implemented within cohort study samples, with regular outcome measurement as part of the cohort data collection. BiBBS participants will be asked to provide consent to be part of a TwiCs study during cohort recruitment. In this case, routinely collected health record data will be used as outcome measurements.

Eligible participants for each intervention chosen for inclusion in a TwiCs evaluation will be identified from the cohort sample. A group will be randomly selected to receive the intervention, and their outcomes will be compared with eligible participants who were not randomly selected. The process can be repeated many times within a cohort, such that a cohort study hosts multiple TwiCs [15].

It is planned that the cohort will host at least three TwiCs evaluations. A rapid consensus exercise has been conducted to identify possible interventions to undergo TwiCs evaluation, based on the current evidence base (i.e. filling a need for generating evidence and not duplicating existing evidence), and on ethical and logistical grounds. Interventions commissioned by BSB may not be withheld from families; however capacity issues may result in some families not receiving an intervention or having to wait to take part. In this context, random selection provides an ethical approach to selecting who takes part. Final decision on eligibility for TwiCs will be made once interventions have been implemented and capacity issues have been assessed. Separate protocols will be prepared for each TwiCs evaluation.

##### Quasi-experimental design

For most of the BSB interventions, random allocation of families will not be possible, due to ethical and logistical constraints. Quasi-experimental methods will be employed to estimate the causal effects of these BSB interventions. We will consider a range of methods, including propensity scores, regression discontinuity and instrumental variables. Quasi-experimental methods are recommended to evaluate interventions or policy changes in ‘real-world’ circumstances where researchers are not able to manipulate which families receive an intervention [12].

Propensity score approaches can be employed for all interventions that have been taken up by a group within the cohort in order to weight or match a balanced control group. Propensity scores (representing the predicted probability that an individual or family will take part in an intervention, given their baseline characteristics) will be calculated using data collected at baseline. The outcomes for the two groups can then be compared. This approach will allow selection bias to be minimised in the analysis, and the causal effects of interventions to be inferred [23, 24]. For example, for participants of an intervention to support women with mental health problems, propensity scores could be calculated to match a control group of women with similar baseline characteristics including depression and anxiety screening scores, socioeconomic status and ethnicity. Outcomes for women who have taken part in the intervention can then be compared with the matched control group to estimate the intervention effects, for example on maternal mental health, mother-child attachment and child development. However, where factors that predict take-up of interventions have not been identified or accurately measured at baseline, there will be residual differences between groups and remaining concerns about selection biases.

Regression discontinuity designs can be used for projects that have an eligibility cut-off for individuals/families, based on a continuous assignment variable (e.g. low BMI, age 19 or lower) [25, 26]. Regression discontinuity approaches will model child outcomes on the assignment variable, to assess whether there is a gap in outcomes (discontinuity) at the eligibility cut-off. Where possible, analysis will be restricted to families/individuals whose assignment variable scores are close to the cut-off, where the intervention can be thought of as randomly assigned (especially if there is measurement error for the continuous variable). The difference in mean outcomes in the groups just above and below the cut-off is the average causal effect. For example, for an intervention targeting teenage pregnancies age at conception can be used as the assignment variable. Outcomes for women either side of the cut off (i.e. age 20) can be compared to estimate the effect of the intervention, for example on breastfeeding initiation or mother-child attachment.

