**Method:**

The BiBBS study aims to recruit 5000 babies, their mothers and their mothers’ partners over 5 years from January 2016-December 2020. Demographic and socioeconomic information, physical and mental health, lifestyle factors and biological samples will be collected during pregnancy. Parents and children will be linked to their routine health and local authority (including education) data throughout the children’s lives. Their participation in BSB interventions will also be tracked. BiBBS will test interventions using the Trials within Cohorts (TwiCs) approach and other quasi-experimental designs where TwiCs are neither feasible nor ethical, to evaluate these early life interventions. The effects of single interventions, and the cumulative effects of stacked (multiple) interventions on health and social outcomes during the critical early years will be measured.

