Baby Steps Antenatal + Postnatal	Antenatal support for women at risk of poor emotional well-being	500	
Family Action Perinatal Peer Support	Peer support for mothers with mild/moderate mental health issues	450	
ESOL+	English language course for parents	950	Communication & Language Development
Postnatal Support			
Infant Mental Health	Professional support for women with poor attachment	200–500	Social & Emotional Development
Northamptonshire Baby Room	Infant brain development course	580	
Incredible Years Parenting ^b^	Parenting programme	1400	
Home-Start	Volunteer support for vulnerable women	225	
Family Links Nurturing	Parenting skills programme for vulnerable families	1050	
Early Years Support			
HENRY	Universal lifestyle programme for parents with young children	1050	Social & Emotional Development /Obesity & Nutrition
Community Nutrition Skills	Cook and eat sessions	1000	Obesity & Nutrition
PiP	Pre-schoolers physical activity in the playground	1500	
Forest Schools	Outdoor play for young children & parents	1500	
Bookstart and Imagination Library	Book gifting service age 0–5	7000	Communication & Language Development
I CAN	Children aged 2 at risk of language delay	675	
Talking Together	Sessions for parents with children aged 2 with language delay	2075	

^a^Evidence based from US study, recently proved non-effective in UK setting

^b^Evidence based intervention (all other interventions are science based)

^c^Estimated number of recipients are taken from the original BSB bid to the BLF. Actual numbers will be finalised within the service design process, based on consideration of local need and service capacity

^d^The specific outcomes for each intervention will be finalised in the service design process

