### Sample size

The BiBBS study aims to recruit 5000 babies over 5 years from January 2016 to December 2021. All women booked for delivery at BTHFT are offered an oral glucose tolerance test (GTT) at 26 to 28 weeks gestation. As 75 % of women attend for the GTT [14] the majority of women and their partners will be recruited in these clinics. For those who do not attend, recruitment will take place in community settings (e.g. at midwife appointments) and at other hospital appointments (e.g. diabetes clinics). Although every effort will be made to find and approach all eligible women, we predict reaching approximately 85 % of the eligible population through these methods. We assume, based on analysis of BiB data [14] and BTHFT data, that:1450 babies are born in the BSB area per year,85 % of pregnant women will be reached and invited to take part (75 % at GTT, 10 % in other settings),80 % of these women will agree to take part.In BiB, the ratio of babies to mothers was 1.11, due to multiple births and multiple pregnancies [14].

As such, we expect to recruit 4930 babies and 4440 mothers over a 5 year period.

Uptake for the partners is likely to be lower and we expect, based on achieved recruitment in BiB, to recruit at least 25 % of partners (*n* = 1125).

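### A propensity score built from pregnancy data cannot balance the reason for entry to programmes triggered by a problem that appears after birth, so their effects are biased downwards

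*Protocol article*

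**What the plan says.** The Quasi-experimental design section gives the propensity score the widest reach of the methods it considers: "Propensity score approaches can be employed for all interventions that have been taken up by a group within the cohort". It defines the score as the probability of taking part given baseline characteristics and says that scores "will be calculated using data collected at baseline". It then says that this minimises selection bias and lets causal effects be inferred. It closes with a general caveat: where predictors of take-up were not identified or accurately measured at baseline, differences between groups will remain.

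Baseline is in pregnancy. The abstract says: "Demographic and socioeconomic information, physical and mental health, lifestyle factors and biological samples will be collected during pregnancy". Most women are recruited at the glucose tolerance test clinic, and the Sample size section gives its timing: "All women booked for delivery at BTHFT are offered an oral glucose tolerance test (GTT) at 26 to 28 weeks gestation". Late presenters are approached on the maternity ward.

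Table 1 lists programmes whose entry reason arises later:

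- Talking Together (2075 estimated recipients): "Sessions for parents with children aged 2 with language delay"
- I CAN (675): "Children aged 2 at risk of language delay"
- Infant Mental Health (200–500, under Postnatal Support): "Professional support for women with poor attachment"

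**The concern.** A propensity score removes selection bias only if it contains what drives entry. For these programmes the driver is an early reading of the outcome domain itself: a child enters a language programme because language is already poor at age 2. That state does not exist when the baseline is taken. Pregnancy data can predict it only in part, so after weighting or matching the controls are still mostly children without the problem. This is confounding by indication, and it works against the programme.

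The section's worked example does not reveal the gap. It concerns maternal mental health, where the baseline can supply depression and anxiety scores.

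Communication and language, and social and emotional development, are two of the study's three outcome domains. A useful programme in either could be reported as having no effect, or as harmful.

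**Working it through.** **The plan's own figure.** The article gives no figure for this bias. Its one computed size reproduces: 1450 × 5 × 0.85 × 0.80 = 4930 babies, and 4930 / 1.11 = 4441 mothers (stated as 4440). The point does not depend on it.

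**Inputs from the article.** Talking Together has 2075 recipients and there are 1450 births a year: 2075 / (5 × 1450) = 2075 / 7250 = 28.6% treated.

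**Assumed inputs (not in the article).**
- Age-2 language score L has SD 1, and baseline explains R² = 0.1 to 0.5 of it.
- The later outcome is Y = ρL + noise + τT (SD 1 before the treatment effect), with ρ = 0.3 to 0.7 and true benefit τ.
- The lowest 40% on L are eligible.
- Strong targeting: 71.5% of eligible children are treated and no others. 0.40 × 0.715 = 28.6%, which matches Talking Together.

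**Method.** 400,000 simulated children per scenario; logistic propensity score on the baseline variables only; controls weighted by p/(1 − p), which gives the effect in the treated.

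**Strong targeting, τ = +0.2 SD, baseline-only score:**

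| R² | ρ = 0.3 | ρ = 0.5 | ρ = 0.7 |
|---|---|---|---|
| 0.1 | -0.175 | -0.425 | -0.668 |
| 0.3 | -0.095 | -0.297 | -0.494 |
| 0.5 | +0.015 | -0.109 | -0.232 |

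Eight of nine estimates are negative. With τ = +0.3 the range is -0.574 to +0.111: six clearly negative, two near zero, and one positive but too small.

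**Mechanism.** The estimate equals τ + ρ × (gap in L left after weighting). For R² = 0.3 and ρ = 0.5 the gap is (-0.297 − 0.2) / 0.5 = -0.99 SD. Put into ρ = 0.7, this gives 0.2 − 0.7 × 0.99 = -0.49, which agrees with the table.

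**Weak targeting, R² = 0.3.** This was run with τ = +0.3. The effect is additive, so subtracting 0.1 gives the result for τ = +0.2:

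| Uptake, eligible / others | ρ = 0.3 | ρ = 0.5 |
|---|---|---|
| 50% / 20% | 0.179 − 0.1 = +0.079 | 0.113 − 0.1 = +0.013 |
| 40% / 20% | 0.219 − 0.1 = +0.119 | 0.168 − 0.1 = +0.068 |
| 35% / 25% | 0.264 − 0.1 = +0.164 | 0.235 − 0.1 = +0.135 |

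All six are too small and none is reversed. A more prognostic trigger could still reverse the first row: the gap is (0.013 − 0.2) / 0.5 = -0.374, and ρ = 0.7 would give 0.2 − 0.7 × 0.374 = -0.06.

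**With the eligibility measure.** Restricting to eligible children and adding L to the score gives +0.19 to +0.21 for τ = +0.2, and +0.29 to +0.31 for τ = +0.3, in every strong-targeting scenario.

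**Control case.** For an antenatal programme whose uptake depends only on measured baseline factors, the baseline score returns +0.30 against a truth of +0.3 (crude difference -0.17). The method works there, so the fault belongs to triggers that arise after baseline.

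**The case against.** The strongest reply is that the article fixes little. The propensity score is one of several methods under consideration, alongside regression discontinuity and instrumental variables, and no section assigns it to a named programme. The Background and Discussion say that methods will be tailored to each intervention as it is designed. The caveat admits residual selection bias, and the Discussion names the comparable control group as a limitation.

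This stands in part. The problem is not wholly unacknowledged, and later covariates are not expressly barred. But the one covariate rule that is stated is the baseline rule. The caveat names no class of programme, no direction and no remedy, and the Discussion's answer is again detailed baseline data plus quasi-experimental methods. Regression discontinuity needs a continuous eligibility measure, and only three or more TwiCs are planned, so the propensity score is the method offered across the board.

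Three stronger readings are tempting but unsupported:

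- **That all twelve postnatal and early-years programmes (5 + 7) are affected.** HENRY is labelled universal, and several others state no post-birth trigger. The vulnerability named for Home-Start and Family Links Nurturing may be visible at baseline. Risk of language delay (I CAN) is partly covered by the baseline language and home literacy items.
- **That the sign is always wrong.** One strong-targeting scenario and all six weak-targeting scenarios above are not negative.
- **That families who moved away distort the control pool.** The Retention section says "Data linkage to GP records ensures that home addresses and the survival status of all participants are regularly updated", but no section says that movers lose access or serve as controls.

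The near-exact recovery with the eligibility measure is also partly built in. The simulation makes uptake random among eligible children and measures the age-2 score without error.

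**Conclusion.** The point holds for programmes entered because of a problem that appears after birth: clearly Talking Together and Infant Mental Health, probably I CAN. For these, the stated covariate rule omits the reason for entry and biases the effect against the programme. For a true +0.2 SD, the illustrative estimates run from -0.67 to +0.02 SD under strong targeting and from about +0.01 to +0.16 SD under weak targeting.

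The direction needs only that the trigger predicts the outcome and that baseline predicts the trigger incompletely. The size, and whether the sign changes, rest on assumed values for targeting, R² and ρ that the article does not give. Antenatal programmes, and universal programmes whose uptake follows baseline factors, are not affected.

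**What to change.** For programmes with a post-birth trigger, change the rule that scores "will be calculated using data collected at baseline" so that they use data recorded up to the date the family became eligible for that intervention. In practice:

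1. Put into the score the pregnancy baseline plus linked measures dated before entry, including the eligibility or screening measure.
2. Draw controls from children or families who met the same criterion at the same age.
3. Where the eligibility measure is not recorded for non-recipients, make no propensity-based causal claim, and rely on a TwiCs evaluation if one is run.
4. Use regression discontinuity only where a continuous eligibility measure is recorded on both sides of the cut-off. It cannot stand in when that measure is missing for non-recipients.

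The cost is more analysis work, a smaller control pool and wider intervals. The loss of precision cannot be sized from the article. Because interventions may not be withheld, eligible non-recipients could be few, and some programmes may lose a propensity-based estimate. Whether linkage will supply the needed measures for non-recipients has to be confirmed, since the figure listing the routine outcome measures is not shown.
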